
### Secondary Outcome Measures

Secondary outcomes include cardiovascular capacity, pulmonary function, grip strength, and self-reported physical and psychosocial health outcomes.

VO_2peak_ (ml/kg/min): VO_2peak_ is measured during a graded exercise test as an indicator of cardiovascular capacity using an arm ergometer (Lode) and open circuit spirometry with a metabolic cart (TruOne, ParvoMedics). Arm ergometers are considered the gold standard modality for exercise testing among people with disabilities who use wheelchairs or cannot run or cycle for prolonged periods [40,41]. Before starting the test, participants rest for 3-5 minutes. They are then instructed to maintain a pace between 55 to 65 revolutions per minute throughout the testing period. The participant starts their test with 2 minutes of warm-up without any resistance, and then the resistance is increased every minute by 10 watts until the participant reaches volitional fatigue or subjective discomfort (eg, shortness of breath and chest pain) or achieves 2 or more of the following termination criteria: age-predicted maximum HR of more than 85%; rate of perceived exertion (RPE) of 8 or more on a 0-10 scale; respiratory energy exchange ratio of 1.1 or higher; or plateau in oxygen consumption [42]. HR and oxygen consumption is measured continuously.FEV1 (forced expiratory volume over 1 second) and FVC (forced vital capacity; liters): Pulmonary function is measured by (1) how much air the participant exhales quickly, and (2) how much air can be expelled after taking a full breath via a portable spirometer (MIR Spirobank). These will be measured 3 times, with a 1-minute resting period between each trial during the testing session.Grip strength (kg): Grip strength is measured using a hand-held dynamometer (Jamar Hydraulic Hand Dynamometer, Lafayette Instruments) for both hands, with 3 trials conducted for each hand and a 1-minute resting period between each trial.Self-reported physical activity (min/wk): The volume of physical activity is measured using the Leisure-Time Physical Activity Questionnaire for SCI [43].Self-reported physical and psychosocial health: Various aspects of physical and psychosocial health are measured using standardized questionnaires by the National Institutes of Health PROMIS (Patient-Reported Outcomes Measurement Information Systems) [44]. This includes Pain Intensity, Pain Interference, Fatigue, Sleep Disturbance, Global Health, Ability to Participate in Social Roles and Activities, Depression, Anxiety, and Physical Function.

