### Aims and Design of this Study

This study’s design includes three aims. The primary aim examines the immediate effect of a 24-week, synchronous M2M-C training protocol compared to a 24-week, asynchronous activity control on core indicators of CMH among 132 adult wheelchair users with ≥2 cardiometabolic risk factors. The secondary aim examines the immediate effect of M2M-C training compared to the active control condition on cardiovascular capacity, physical activity, and quality of life. The first tertiary aim evaluates the sustained effects of M2M-C training (24 to 36 wk) on physical activity participation. A second tertiary aim evaluates the potential response heterogeneity in CMH, cardiovascular capacity, and physical activity outcomes using prespecified moderator variables (eg, age, sex, body composition, diet, or ethnicity) to understand for whom the intervention is most effective.

This study’s aims will be tested using a parallel-group, assessor-blinded RCT design. For primary and secondary aims, we hypothesize that a telehealth M2M-C program will lead to significantly greater improvements in CMH outcomes, peak oxygen consumption (VO_2peak_), physical activity level, and quality of life from baseline to 24 weeks compared to controls. For the tertiary aim 1, we hypothesize that M2M-C participants will maintain physical activity levels from week 24 to week 36.

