### Power Analysis and Sample Size

We plan to recruit 132 participants into this study (66 per treatment group), with the expectation that at least 100 (50 per group) will complete this study. We anticipate an attrition rate of 23% based on the average attrition rate between the largest home-based behavioral interventions among wheelchair users (33%) [13] and our scoping review of exercise trials for people with various disabilities (13%) [14]. Due to the nature of the proposed exercise training involving one-on-one training and supervision, we believe that the role of exercise training coaches in this study will lead to lower attrition rates as it has in our past studies [26].

Power calculations were performed using nQuery (version 8.5; Statsols). For the primary outcome of CMH, we obtained SDs of biomarkers of this outcome from our pilot study among individuals with SCI (6-wk arm crank exercise training), including SDs of 43 mg/dL for total cholesterol, 4.3% for body fat, and 22.4 mg/dL for triglycerides [27]. Assuming a final sample size of 50 participants per group, a 2-sided 2-group *t* test (2-tailed), and a significance level of .05, we will have at least 80% power to detect differences of 24.4 mg/dL for total cholesterol, 2.5% for body fat, and 12.7 mg/dL for triglycerides (and greater) between the intervention and control groups as being statistically significant. This is equivalent to detecting an effect size (Cohen *d*) of 0.566 (a moderate effect size) as statistically significant between the two groups.

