### Primary Outcome Measures

CMH outcomes are assessed via venipuncture blood specimen, brachial cuff BP, and body composition.

High sensitivity C-reactive protein (hsCRP; mg/L): hsCRP is a critical marker of inflammation that contributes to proinflammatory and prothrombotic elements of cardiovascular risk. A single hsCRP measure is a strong predictor of myocardial infarction or coronary heart disease mortality and several other diseases of the circulatory system in people without a history of such conditions [28]. Changes in hsCRP may occur from as early as 8 weeks of exercise [29].Hemoglobin A1c (HbA1c, mmol/mol): HbA1c is a measure of red blood cell mean hemoglobin glycation over the previous 3 months. Exercise interventions without a dietary component should yield a small to moderate effect on HbA1c after a month of training [30].Fasting insulin (μIU/mL): A high fasting insulin level indicates the presence of insulin resistance and whether an individual shows glucose intolerance. Exercise interventions without a dietary component should yield a small beneficial change in fasting insulin levels after a month of training [30].Fasting glucose (mmol/L) and homeostatic model assessment of insulin resistance: This is calculated as [fasting insulin (μU/mL) × fasting glucose (mmol/L)]/22.5 [31].Fasting triglycerides (mg/dL): A triglyceride level >150 mg/dL, is largely supported as an indicator of cardiovascular risk [32,33]. Exercise interventions without a dietary component should yield a small beneficial change in triglyceride levels after a month of training [30], even among people with normal triglyceride levels [34].Fasting cholesterol (mg/dL): Abnormalities in the lipid profile, including elevated total and LDL cholesterol as well as decreased HDL cholesterol, are predictors of future cardiovascular disease among young and middle-aged people [35,36]. Exercise interventions without a dietary component should yield a small effect after 1 month [30].BP (mmHg): Moderate-intensity exercise has been shown to reduce BP [37].Waist circumference (cm): The waist circumference is measured at the level of the superior border of the iliac crest, above the umbilical level, and at the midline level [38] using a Gulick tape.BMI (kg/m^2^): Dual-energy x-ray absorptiometry (DXA) scan is used to measure weight-adjusted BMI, in addition to total mass, lean mass, and fat mass. It is evident that people with SCI often have elevated waist circumference (≥94 cm), but their BMI is less than 30 kg/m2[39].

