## Discussion

### Principal Findings

The CHIME study proposes a parallel-group RCT for examining the 24-week effects of an evidence-based M2M program compared with a control condition for yielding immediate and sustained CMH outcomes among adult wheelchair users with poor cardiometabolic profiles. This study anticipates that after 24 weeks, participants in the M2M-C intervention group will show significant improvements in key cardiometabolic risk factors, such as reduced HbA_1c_ levels; lower fasting glucose and triglycerides; and decreased BP, waist circumference, and body fat percentage, compared to the control group. Furthermore, the M2M-C intervention is expected to improve health-related physical fitness, including measurements such as VO_2peak_, FEV1, FVC, and grip strength, in line with self-reported psychosocial health outcomes. In addition to the improvements in CMH and physical fitness, we anticipate that these benefits will be sustained during the maintenance phase (up to 36 wk). This suggests that wheelchair users may be able to adhere to telehealth-based exercise programs over the long term. If successful, this study will be the largest and sufficiently powered confirmatory RCT trial targeting CMH outcomes in this population. The prescribed exercise dose was informed by the review of the relevant literature [22]. If successful, this study will establish an evidence-based recommendation of adequate exercise dosing for adult wheelchair users with poor CMH profiles.

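### Cardiovascular capacity is scored only as VO2peak per kg of body mass on an arm-crank test, so net weight loss at unchanged oxygen uptake would register as a capacity gain

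*Protocol article*

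**What the plan says.** All references are to the protocol article.

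- **The outcome.** Secondary Outcome Measures defines it thus: "VO_2peak_ (ml/kg/min): VO_2peak_ is measured during a graded exercise test as an indicator of cardiovascular capacity using an arm ergometer". Of the test signals it adds: "HR and oxygen consumption is measured continuously". No version in L/min or per kg of lean mass is named, and peak power is not listed as an outcome.
- **The hypothesis.** Aims and Design of this Study treats cardiometabolic health (CMH) as the primary aim and cardiovascular capacity as part of the secondary aim. For both it expects "significantly greater improvements in CMH outcomes, peak oxygen consumption" relative to control, from baseline to 24 weeks.
- **Body composition.** Primary Outcome Measures uses DXA for BMI, "in addition to total mass, lean mass, and fat mass". Power Analysis and Sample Size takes "SDs of 43 mg/dL for total cholesterol, 4.3% for body fat, and 22.4 mg/dL for triglycerides" from a pilot study and derives detectable differences of "24.4 mg/dL for total cholesterol, 2.5% for body fat, and 12.7 mg/dL for triglycerides". Principal Findings anticipates "decreased BP, waist circumference, and body fat percentage, compared to the control group", and separately anticipates a rise in VO2peak.

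**The concern.** A score in ml/kg/min is a ratio. It rises when oxygen uptake rises, and also when body mass falls. On an arm ergometer the participant works against a set resistance and does not carry body weight, so the divisor does not represent the work done. The trial also expects the intervention to reduce body fat, which would lower the divisor unless lean mass rose to offset it.

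A body-composition effect, which belongs to the primary aim, can therefore pass arithmetically into the capacity outcome of the secondary aim. The direction favours M2M-C if, as expected, that arm loses more fat. Randomisation and blinded assessors do not prevent this, because it arises from changes after allocation. The baseline covariates and moderators listed for the models do not remove it either. At stake is the interpretation of a secondary outcome: a between-group gain in ml/kg/min could reflect better oxygen uptake, lower mass or both, and the stated variable alone cannot tell them apart.

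**Working it through.** **Inputs from the article.** 50 completers per group, two-sided 5% level, body-fat SD 4.3%, detectable body-fat difference 2.5%, effect size 0.566 (Power Analysis and Sample Size); VO2peak in ml/kg/min (Secondary Outcome Measures).

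**Assumption.** Baseline body fat is not given, so a range of 25% to 50% is used.

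**Step 1: the plan's own figure.** The two-sample t test power (noncentral t, 98 df) at d = 0.566 with 50 per group is 80.0%. For body fat, 2.5/4.3 = 0.581, which gives 82.1%. The exact detectable effect is d = 0.5659, or 0.5659 × 4.3 = 2.43. The stated figure reproduces. It follows from the sample size and the SD and carries no prediction of how much fat will be lost.

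**Step 2: the ratio.** Let V be absolute VO2peak, L fat-free mass and f the fat fraction. Total mass is L/(1 − f), so the score is V(1 − f)/L. With V and L unchanged and f moving from f1 to f2:

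relative change in score = (1 − f2)/(1 − f1) − 1 = (f1 − f2)/(1 − f1)

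**Step 3: size with lean mass and L/min constant.**

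| Baseline fat | Fall of 2.5 points: 0.025/(1 − f) | Fall of 2.5% relative: 0.025f/(1 − f) |
|---|---|---|
| 25% | 3.3% | 0.8% |
| 30% | 3.6% | 1.1% |
| 35% | 3.8% | 1.3% |
| 40% | 4.2% | 1.7% |
| 45% | 4.5% | 2.0% |
| 50% | 5.0% | 2.5% |

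The percentage-point reading is the more natural one, because the SD of 4.3% is given as an SD of body fat. The article does not say so outright.

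**Step 4: if lean mass rises by a fraction g.** For a 2.5-point fall, the change is (1 − f + 0.025)/[(1 − f)(1 + g)] − 1. At f = 40%:

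- g = 1%: 0.625/0.606 − 1 = 3.1%
- g = 2%: 0.625/0.612 − 1 = 2.1%
- g = 3%: 0.625/0.618 − 1 = 1.1%

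If total mass does not change, the effect is 0%.

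**Step 5: illustration (invented participant).** At 90 kg, 40% fat and 1.35 L/min, the score is 1350/90 = 15.0 ml/kg/min and lean mass is 54 kg. At 37.5% fat and the same lean mass, weight is 54/0.625 = 86.4 kg and the score is 1350/86.4 = 15.6, a rise of 4.2%. Scored in L/min, the change is zero.

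These are changes within one participant. The between-group distortion reflects the difference between arms in mass change, so equal proportional loss in both arms would largely cancel.

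**The case against.** **Scaling is a choice, and the article is condensed.** Nothing in the text is contradictory: a per-kg VO2peak is a recognisable outcome and eases comparison with published per-kg values. Oxygen consumption and DXA masses are recorded, so an unseen full protocol or analysis plan may already specify L/min. This stands to the extent that the absence of a supporting analysis is not itself a fault. It does not dispose of the point, because the article does fix a unit, and that unit responds to an expected effect of the intervention.

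**The aim is not worded as independent of body composition.** A reader might infer that the secondary aim promises a capacity effect separate from fat loss. The article says only that it will examine or explore effects on capacity. The objection is right, and the fix is therefore confined to what may be claimed.

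**The size may be small.** A reader might also infer that the trial will count a gain of about 4%. That needs a 2.5-point loss, an assumed baseline fat near 40%, constant lean mass and unchanged L/min, all together. An energy budget for the illustrative participant suggests less:

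- Table 1 sums to 3 × (250 + 14 × 40) = 2,430 aerobic minutes, or 3 × (350 + 14 × 50) = 3,150 exercise minutes.
- Assume 5 kcal per litre of oxygen, 7,700 kcal per kg of fat and work at 70% of 1.35 L/min, or 0.945 L/min. None of these is in the article.
- Then 2,430 × 0.945 × 5 = 11,482 kcal (1.5 kg) and 3,150 × 0.945 × 5 = 14,884 kcal (1.9 kg). The score rises by 90/88.5 − 1 = 1.7% to 90/88.1 − 1 = 2.2%.
- Even all 3,150 minutes at full peak uptake give 3,150 × 1.35 × 5 = 21,263 kcal, or 2.8 kg, short of the 3.6 kg in Step 5.

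Subtracting resting expenditure, or loss in the exercising control group, would lower this. Spontaneous diet change could raise it. The check limits the size but leaves the mechanism intact.

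**Conclusion.** The concern holds in a limited form. The only capacity variable the article names is divided by body mass on a test that does not carry body mass, and more fat loss is expected in one arm. Net mass loss at unchanged oxygen uptake would then score as a capacity gain.

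The size is conditional: 3.3% to 5.0% for a 2.5-point fat loss with constant lean mass at 25% to 50% baseline fat, roughly 1% to 3% if lean mass rises or the 2.5% is relative, and 0% at unchanged mass. The documents support no single figure within that range.

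Three stronger readings should be resisted. The 2.5% is a detectable difference, so fat loss of that size cannot be presumed. The per-kg score is not an error and need not be dropped. VO2peak is a secondary outcome, so neither the sample size nor the primary analysis is touched. The change is still worth making, because the possible bias favours the intervention and removing it costs almost nothing.

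**What to change.** Name two VO2peak variables before results are known: absolute VO2peak in L/min, analysed with baseline L/min in the model, and the existing ml/kg/min. State that improved cardiovascular capacity independent of weight change will be claimed only if the L/min result supports it. Report VO2peak per kg of DXA lean mass as a supporting value. If only ml/kg/min improves, the report should say that the gain may reflect weight change.

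Requiring L/min to agree adds a condition to the claim, so it does not raise the false-positive rate. Absolute uptake comes from the metabolic cart and the masses from DXA, so no new test, visit or participant burden arises. The cost is a sentence or two in the plan, one more derived variable, and slightly less direct comparability with published per-kg values for the L/min result. With 16 participants recruited by August 2024 and data collection expected to run to November 2027, there was ample time at the article's date to prespecify this.

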
### Moderating Outcome Measures

The moderating outcome measures are as follows:

Demographics and clinical characteristics of participants (eg, age, sex, ethnicity, diagnosis, or medications)Exercise behavior measured by Exercise Self-efficacy Scale [45,46], and Exercise Goal Setting and Planning Scale [47] based on Social Cognitive Theory constructsSelf-reported diet using the Rapid Eating Assessment for Participants Shortened Version [48,49]Exercise enjoyment using the Physical Activity Enjoyment Scale [50] and satisfaction via qualitative, semistructured one-on-one interviewExercise session duration based on attendance rate and video minutes viewed via online platform analyticsExercise intensity based on minutes exercised at moderate-to-vigorous intensity using an optical HR monitor (Polar Verity Sense, Polar) and RPE scale 0-10: The RPE is periodically asked during the exercise session to adjust the intensity and at the end of the exercise session to obtain the overall exertion level. The talk test is used as a secondary measure, primarily to ensure that participants stay in the moderate-to-vigorous intensity training zone and that RPE is related to aerobic strain as opposed to anaerobic. Additionally, this is an important indicator of exercise intensity, especially for individuals with a blunted exercise HR response.

### Random Assignment

After participants are determined eligible and all baseline assessments are complete, they are randomized into 1 of the 2 groups, M2M-C or control (n=66 per group), with a 1:1 allocation ratio. The randomization sequence is generated and only known by the project statistician using a computer-generated random schedule in permuted block (SAS; version 9.4; SAS Institute Inc). The block size is unknown to intervention staff.

### Intervention Arm—Home-Based, Synchronous Aerobic Exercise Training Using M2M

The prescriptive exercise guideline in this proposed study was generated through a critical review of the relevant literature. To determine an appropriate exercise dose, we used data from 16 studies of moderate-intensity aerobic exercise included in a recent meta-analysis on CMH effects of exercise training in the general population [22]. Specifically, we calculated the total prescription (average prescription per week × intervention duration) for each study and the overall average. We determined that an aerobic exercise training dose of approximately 2400 minutes (40 h) over 6 months would be necessary for CMH benefits. We then spread the minutes across a 24-week intervention period for this trial with wheelchair users to ensure adequate time to safely and progressively reach the prescribed dose. The session structure and exercise minutes for each week are presented in Table 1, and the intervention components are summarized in Table 2.

**Table 1 table1:** Movement-to-music cardiovascular session structure and exercise in minutes for each week.

Week	1	2	3	4	5	6	7	8	9	10	11-24
Checking in	5	5	3	3	3	3	3	3	2	2	2
Range of motion	5	5	5	5	5	5	5	5	5	5	5
Aerobic	15	15	20	20	25	25	30	30	35	35	40
Cool down	5	5	5	5	5	5	5	5	5	5	5
End discussion	5	5	5	5	5	5	5	5	3	3	3
Exercise min/session	25	25	30	30	35	35	40	40	45	45	50
Total min/session	40	40	45	45	50	50	55	55	60	60	60

**Table 2 table2:** Summary of movement-to-music cardiovascular program features.

Feature			Description
**Prescription**			2400 minutes of exercise across 24 weeks Progressive Individualized
**Frequency**			3 times per week
**Session duration**			25 to 50 minutes
**Intensity**			Moderate-to-vigorous Maximum heart rate at or above 70% Rate of perceived exertion between 3 and 7
**Intervention length**			24 weeks
**Setting**			Home
**Exercise mode**			Aerobic using M2M^a^
**Supervision**			
	Who	M2M instructors Assistant telecoaches	
	Mode	Remote telecoaching	
	Oversight	Zoom (Zoom Communications, Qumu Corporation) and TeleRehab app (JNP Enterprises LLC) Live, instruction sessions with M2M instructors Monitoring sessions with assistant health coaches using recorded live session videos	
**Meeting with the instructor or coach**			
	Weeks 1-8	1× M2M instructors 2× assistant telecoaches	
	Weeks 9-16	1× M2M instructors 1× assistant telecoaches 1× self-guided with no supervision	
	Weeks 17-24	1× assistant telecoaches 2× self-guided with no supervision	
**Equipment provided**			Computer tablets Tablet stand Polar heart rate monitor
**Intervention safety**			Zoom oversight Adverse event or serious adverse event reporting

^a^M2M: movement to music.

During the 24-week training phase, the M2M-C group receives 1:1 synchronous training from M2M-trained exercise instructors and assistant health coaches within a remotely coached, home-based setting using telehealth monitoring platforms (ie, Zoom, TeleRehab app). The intervention is administered 3 times per week, starting at 25 minutes per session and increasing by 5 minutes every 2 weeks to a maximum of 50 minutes. The exercise program focuses on improving cardiorespiratory fitness using a series of movement patterns accompanied by music. The program is tailored to an individual’s functional abilities (eg, use lower limb if able, slow vs fast tempo, level of trunk control) and preference of musical themes, including classical, country, decades (oldies), international, jazz or blues, and pop.

For the first 8 weeks of the training phase, participants attend 1 instructional session with an M2M instructor per week, and the live session is video-recorded via Zoom. Participants attend 2 monitoring sessions in the same week to repeat the exercise using the prerecorded video of the week with assistant telecoaches. For the second 8 weeks (wk 9-16), participants continue to attend 1 instructional session with an M2M instructor per week, and the live sessions are video recorded. Participants attend 1 monitoring session with assistant telecoaches and 1 self-guided session without any supervision. For the third 8 weeks (wk 17-24), participants no longer meet with M2M instructors. Using the recorded videos between weeks 11 and 16 (ie, 40 minutes per video; archived with no instructions), participants attend 1 monitoring session per week with assistant telecoaches and 2 self-guided sessions in the same week.

